### Participants

2.2

Potential study participants will be identified through comprehensive ophthalmic examination. Informed consent will be given to the eligible participants and they will be given time to think about their participation and ask questions about the study; if approved, the participant will be recruited into this study.

### Inclusion criteria

2.3

Eligible participants will have Type 2 diabetes and DME, as determined by SD-OCT, in 1 or both eyes with either:

CST of > 300 microns as determined by SD-OCT due to DME or

CST of < 300 microns provided that intraretinal and/or subretinal fluid is present in the central subfield (central 1 mm) related to DME

Have visual acuity of > 24 early treatment diabetic retinopathy study (ETDRS) letters (Snellen equivalent > 20/320)

Be amenable to laser treatment, as judged by the treating ophthalmologist

Be over 18 years of age

### Exclusion criteria

2.4

Ineligible for IVC treatment, as judged by the treating ophthalmologist

Has severe PDR requiring surgery

Has received intravitreal anti-VEGF therapy or steroids within the previous 3 months

Has received retinal laser treatment within the previous 3 months

Has had cataract surgery within the previous 6 weeks

Has glaucoma, retinal vein occlusion, uveitis, optic nerve disease, or other fundus diseases except DME

Has severe cardiovascular, cerebrovascular, liver, and hematopoietic system diseases, and diabetic nephropathy with renal failure

Has serious life-threatening primary disease or mental illnesse

Are pregnant or breastfeeding

Are participating in clinical trials of other drugs

### Outcome measures

2.5

#### Primary outcome

2.5.1

Mean change in BCVA on the study eye at both 24 and 48 weeks following treatment

#### Secondary outcomes

2.5.2

Mean change in CST in the study eye from baseline to both 24 and 48 weeks

Mean change in retinal microvascular metrics by optical coherence tomography angiography (OCTA)

Occurrence in the percentage (%) of side effects from baseline to 48 weeks

Number of injections performed

Use of additional treatments

### Randomization

2.6

All participants will be randomised 1:1 using computer-generated randomization, with sequentially numbered, to receive either 3 + PRN or 6 + PRN treatment. All participants are single-masked of the allocation and regimen after randomization. Randomization is advised to be conducted on the day of IVC treatment.

### Interventions

2.7

All patients in 3 + PRN group will receive a minimum of 3 initial monthly IVC (0.5 mg) injection, PRN dosing thereafter BCVA and CST stabilization criteria-driven PRN treatment while 6 + PRN group will receive a minimum of 6 initial monthly IVC (0.5 mg) injection, PRN dosing thereafter BCVA and CST stabilization criteria-driven PRN treatment.

### Study procedures

2.8

#### Patient evaluation

2.8.1

All participants will be assessed from baseline to 48 weeks according to the schedule of assessments (Table 1). Primary outcome, BCVA will be measured ETDRS visual acuity charts at 4 m at baseline and at months 1, 3, 6, and 12. Secondary outcomes, CST will be measured ETDRS visual acuity charts at 4 m at baseline and at months 1, 3, 6, and 12, while OCTA will be checked at 6 and 12 months.

**Table 1 T1:**
[figure not shown]
Assessment protocol for the current study.

#### Data collection

2.8.2

Case report form (CRF) will be used to collect data for this study.

### Quality control

2.9

(1)Observation ophthalmologists will receive pre-clinical training, have a full understanding of the specific content of the clinical trial program, and check and record according to the time and method specified in the program.(2)Special personnel regularly check the progress of clinical trials, and convene clinical interim meetings to ensure that trials are conducted in accordance with the protocol, drug clinical trial management regulations, and related regulations.(3)The inspection center and other relevant departments establish standard operating procedures and quality control procedures.(4)Establish a test coordination committee. The coordination committee is responsible for the implementation of the entire test and studies and solves the problems related to the test.

### Sample size

2.10

This study is powered to demonstrate non-inferiority of 6 + PRN with respect to the effective rate (at 48 weeks). The trial will have sufficient statistical power to determine superiority of 6 + PRN treatment over the 3 + PRN. According to our clinical application, we initially expect the effective rate of IVC for DME to be around 75%. After calculation, 50 cases are required for each group. Considering the shedding rate of 20%, 60 cases are required for each group, and a total of 120 cases for the 2 groups.

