### Statistical analysis

2.11

SPSS statistical software (IBM Statistics, v. 22.0; IBM Corp, Armonk, NY) will be used to conduct analysis. Quantitative data, BCVA, is represented by median (quartile), and other data is represented by mean and SD. The comparison of clinical features between groups was performed using the *t* test. Changes in BCVA before and after treatment were tested using Wilcoxon–Matt–Whitney test. The change of CST and indicators of retinal blood flow from baseline were analyzed by paired *t* test. The comparison of different follow-up time indicators was performed by repeated measurement data analysis of variance. Statistical significance will be based on 2-sided tests, with *P* value less than .05 taken as the criterion for statisticalsignificance.

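### The sample size rests on an undefined effective rate instead of the primary outcome, mean BCVA change, and the claim of sufficient power for superiority is unsupported

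*Protocol article*

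**What the plan says.** Section 2.5.1 defines the primary outcome as "Mean change in BCVA on the study eye at both 24 and 48 weeks following treatment", which is continuous. The secondary outcomes in Section 2.5.2 are CST change, OCTA metrics, the percentage with side effects, the number of injections and additional treatments.

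Section 2.10 sizes the trial on something else: "This study is powered to demonstrate non-inferiority of 6 + PRN with respect to the effective rate (at 48 weeks"). It then claims more: "The trial will have sufficient statistical power to determine superiority of 6 + PRN treatment over the 3 + PRN". The only numerical assumption about effect is "we initially expect the effective rate of IVC for DME to be around 75" per cent. The result is "After calculation, 50 cases are required for each group", followed by "Considering the shedding rate of 20%, 60 cases are required for each group, and a total of 120 cases for the 2 groups".

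Section 2.1 labels the trial an equivalence trial. Section 2.11 names t tests, a Wilcoxon-type rank test for BCVA change, paired t tests and repeated-measures analysis of variance. On the error rate it says "Statistical significance will be based on 2-sided tests, with *P* value less than .05".

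**The concern.** The quantity that fixes the sample size and the quantity that answers the trial's question are different, and nothing in the text links them. The effective rate has no definition, no place in the outcome list and no analysis. The primary outcome has no difference, margin or SD behind it in Section 2.10.

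The superiority sentence adds to this. Power for superiority is a function of an assumed difference, and a single rate for the drug supplies none. At stake is how the result will be read. If the arms do not differ significantly on BCVA, Section 2.10 invites the reader to take that as the result of an adequately powered superiority trial, although the article contains no calculation to support this.

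**Working it through.** **Inputs from the article.** Effective rate 75%; 50 evaluable per arm; 20% loss; 60 enrolled per arm (all Section 2.10); 1:1 allocation (Section 2.6); two-sided 5% (Section 2.11), taken as one-sided 2.5% for non-inferiority.

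**Assumptions, not in the article.** Target power 80%; the margin; the difference between arms; the arm to which 75% applies; the SD of BCVA change.

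**1. Can 50 per arm be reproduced?** Not from the stated inputs, because margin and power are missing. With 75% in both arms, n per arm = 2 × 0.75 × 0.25 × (1.960 + 0.842)² / margin². This gives 295, 131, 74 and 48 per arm for margins of 10, 15, 20 and 25 points. Solved for the margin at n = 50: 2.802 × √(0.375/50) = 2.802 × 0.0866 = 0.243, or about 24 points. The power of 50 per arm, Φ(margin/0.0866 − 1.960), is 21%, 41% and 64% for margins of 10, 15 and 20 points.

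**2. Superiority on the effective rate.** Pooled z test, 50 per arm: power = Φ[(Δ − 1.960 × √(2p̄(1−p̄)/50)) / √((p₁(1−p₁) + p₂(1−p₂))/50)], where Δ is the difference and p̄ the mean of the two rates. With 75% against 85%: (0.10 − 1.960 × 0.0800)/0.0794 = −0.716, so power is 24%.

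| 6+PRN rate, with 3+PRN at 75% | Power, 50 per arm | Power, 48 per arm |
|---|---|---|
| 80% | 9% | 8% |
| 85% | 24% | 23% |
| 90% | 51% | 49% |
| 95% | 81% | 79% |

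For 80% power, 250 per arm are needed against 85% and 100 per arm against 90%. If 75% is instead the 6+PRN rate, 50 per arm reaches 80% power only when the 3+PRN rate is about 48% or lower.

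**3. Dropout.** 50/(1 − 0.20) = 62.5, so 63 per arm. The stated 60 equals 50 × 1.2, and 60 × 0.80 = 48.

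**4. The primary outcome.** With 48 evaluable per arm, two-sided 5% and 80% power, the normal approximation is 2.802 × √(2/48) = 0.572 SD; the t test needs 0.578 SD. For a rank test under normality, 0.578/√0.955 = 0.59 SD. In letters, with the t test, 0.578 × SD is 4.6, 5.8 or 6.9 for assumed SDs of 8, 10 or 12. Turned round, power for an assumed 5-letter difference with 48 per arm (normal approximation) is 87%, 69% and 53% at those SDs.

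**The case against.** The strongest reply is that Section 2.10 opens with non-inferiority, and one common rate is the normal input for a non-inferiority calculation. A 25-point margin with 80% power gives 48 per arm, close to the stated 50. This stands: the lack of an assumed difference is no fault in how 50 was reached, and it bears only on the superiority sentence.

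A condensed article may also leave the margin, target power and SD to the full protocol. Taken alone, those gaps are not the point. Nor is the lack of a named test for proportions decisive by itself, since the side-effect percentage has none either. What remains is a conflict that a fuller document could not remove without changing one side: the sizing endpoint is not the primary outcome and is not an outcome at all.

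A reader might go further and infer that superiority power does not exist, or that the claim is false for any realistic gain. The article does not support that. Power is about 81% for 75% against 95%, and for BCVA it depends on a difference and an SD that are not given. With an SD of 8 letters, a 5-letter difference would have adequate power. Nor does the article say which gain is realistic.

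**Conclusion.** The concern holds on two counts. First, the sample size is justified on an endpoint that the trial neither defines, lists nor analyses, so it says nothing about the power of the primary comparison. Second, the superiority sentence is unsupported, which is not the same as disproved. With 75% as the 3+PRN rate it holds only for a gain of about 20 points; with 75% as the 6+PRN rate it needs 3+PRN at about 48% or lower. The article assigns the 75% to neither arm, so both readings are assumptions.

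Non-inferiority fares little better. With 75% in both arms, one-sided 2.5% and 80% power, 50 per arm corresponds to a margin of about 24 points that the article does not state. The dropout allowance also falls short of the article's own requirement, by 2 patients per arm. The letter figures for BCVA rest on assumed SDs.

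**What to change.** Keep 120 patients and rewrite Section 2.10.

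- State one objective. Equivalence in Section 2.1 and non-inferiority and superiority in Section 2.10 must be reconciled.
- Base the section on mean BCVA change at one named primary time point. Section 2.5.1 at present names both 24 and 48 weeks.
- If the objective is a between-arm difference, state that 48 evaluable per arm gives 80% power at two-sided 5% for about 0.58 SD with a t test, or about 0.59 SD with the rank test of Section 2.11. Use the figure for the test that will be applied, and give the letters it means at a declared SD.
- If the objective is non-inferiority, state the BCVA margin and the power that 48 per arm gives for it.
- Give 48, not 50, as the number expected to be evaluable.
- Delete the superiority sentence, or replace it with actual power figures and the differences they assume.
- If the effective rate is kept, define it, list it in Section 2.5.2 and compare it between arms by a risk difference with a 95% confidence interval.

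The cost is protocol wording and no extra patients. The stated power becomes less favourable. The Discussion reports 28 eyes recruited by 6 July 2020, so at that date the change could still be made early in recruitment.

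### The allowance for dropout is miscalculated: at the plan's own 20% loss, 60 cases per group leave 48, not the 50 stated as required

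*Protocol article*

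**What the plan says.** All the figures are in section 2.10 (Sample size) of the protocol article. The trial is sized on an effective rate at 48 weeks, expected to be about 75%, with non-inferiority as the stated objective and a further claim of adequate power for superiority. The section gives the result of the calculation as "After calculation, 50 cases are required for each group". It then makes the allowance for loss: "Considering the shedding rate of 20%, 60 cases are required for each group, and a total of 120 cases for the 2 groups". Section 2.6 (Randomization) fixes equal allocation: "All participants will be randomised 1:1 using computer-generated randomization". No other section defines the loss rate differently or gives another rule for enlarging the sample.

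**The concern.** The section gives three numbers that should fit together: the number needed, the expected loss and the number to enrol. They do not. Because the plan raises 50 to 60 to cover loss, it treats 50 as the number that must remain. With 60 enrolled and the stated loss, fewer than 50 remain.

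What is at stake is a headline design figure. As written, the section tells the reader that enrolling 120 protects the required number against 20% loss, and it does not. Whatever power the authors attach to 50 per group would be slightly lower at the number actually expected.

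**Working it through.** **Inputs, all from the protocol article**

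- Required per group: n = 50 (section 2.10)
- Loss rate: d = 20% (section 2.10)
- Enrolled: 60 per group, 120 in total (section 2.10)
- Allocation: 1:1 (section 2.6)

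**1. Reproducing the plan's figure**

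n × (1 + d) = 50 × 1.20 = 60 per group; 2 × 60 = 120. This matches the article exactly.

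**2. The allowance that a 20% loss calls for**

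Loss is a fraction of those enrolled, so N × (1 − d) must be at least n, and N = n / (1 − d) = 50 / 0.80 = 62.5. Rounded up, this is 63 per group, or 126 in total. Check: 63 × 0.80 = 50.4, which meets 50. Rounding does not explain the 60.

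**3. What 60 per group delivers**

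- Expected to remain: 60 × 0.80 = 48 per group, 96 in total
- Shortfall: 50 − 48 = 2 per group, 4 in total, or 2/50 = 4%
- Largest loss that still leaves 50: 1 − 50/60 = 16.7%

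**4. Effect on power, under assumptions**

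The article gives neither a power level nor a non-inferiority margin. I therefore assume that 50 per group was chosen to reach a conventional power, with a true rate of 75% in both groups, and use the normal approximation.

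- Standard error of the difference at 50 per group: √(2 × 0.75 × 0.25 / 50) = 0.0866
- Standard error at 48 per group: √(2 × 0.75 × 0.25 / 48) = 0.0884
- Implied margin: (z for alpha + z for power) × 0.0866
- Power at 48: Φ(margin / 0.0884 − z for alpha)

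| One-sided alpha | Assumed power at 50 | Implied margin | Power at 48 |
|---|---|---|---|
| 0.025 | 80% | 0.243 | 78.4% |
| 0.025 | 90% | 0.281 | 88.8% |
| 0.05 | 80% | 0.215 | 78.6% |
| 0.05 | 90% | 0.253 | 88.9% |

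The loss of power is between 1.1 and 1.6 percentage points. Section 2.11 (Statistical analysis) specifies two-sided tests at 0.05, which corresponds to the one-sided 0.025 rows. The implied margins only carry the calculation; they are not the authors' margins.

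**The case against.** The strongest reply is that this hardly matters. The 20% is a round planning guess, the gap is 2 cases per group, and a loss just below the guess (16.7% or less) would still leave 50. No conclusion of the trial is likely to turn on it. That stands, and it sets the severity.

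A second reply is that the 20% could mean an addition of 20% to the required number, which would give 60. Nothing in the article defines it that way. On that reading the loss covered is 10 of 60, or 16.7% of those enrolled, so the section would still need rewording.

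A reader might also infer more than the article supports:

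- **A loss of precision for BCVA.** The shortfall could be turned into a larger detectable difference in BCVA change. Section 2.10 does not size the trial on BCVA, and such a figure would bring in an outcome, a test and a power level that the section does not use.
- **A complete-case analysis that makes the loss direct.** Section 2.11 states no rule for missing data, and that rule is commonly left to the analysis plan, which is not shown. The point does not need it, because section 2.10 itself treats 50 as the number left after loss.
- **A false numerical power claim.** The article says only that power is sufficient. There is no figure to call wrong.

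**Conclusion.** The point holds as an arithmetic error within section 2.10. The stated enrolment does not deliver the stated requirement at the stated loss: 48 per group against 50. This rests only on the article's own three numbers and on reading a loss rate as a fraction of those enrolled.

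The size is small: 2 evaluable cases per group, or 3 more enrolled per group to make it good. The power figures depend on the assumed 80% or 90% and the assumed equal rates of 75%, and show only the order of magnitude.

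The error does not show that the trial is underpowered, since the derivation of the 50 cannot be checked without a margin and a power level. Severity: minor.

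**What to change.** Either of two changes makes the section consistent.

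1. **Keep 120 and state what it yields.** Suggested wording: *Sixty cases per group (120 in total) will be randomised. At 20% loss, 48 cases per group are expected to be evaluable; 50 per group are retained only if loss does not exceed 16.7%.* Then give the power for non-inferiority and for superiority on the effective rate at 48 per group, with the margin and rates used. Without that power statement, the sentence requiring 50 would still contradict the expected 48.
2. **Keep 50 and correct the enrolment figure** to 63 cases per group, 126 in total.

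The first option costs a few sentences and a slightly less favourable power figure, with no extra recruitment. The second costs 6 more cases in total. Section 3 (Discussion) reports 28 eyes recruited by July 6, 2020, so at that date either change was practicable. The suggested wording keeps the article's term, cases, because section 2.10 does not say whether a case is a patient or an eye and this correction should not settle that.

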### Statistical analysis

2.11

SPSS statistical software (IBM Statistics, v. 22.0; IBM Corp, Armonk, NY) will be used to conduct analysis. Quantitative data, BCVA, is represented by median (quartile), and other data is represented by mean and SD. The comparison of clinical features between groups was performed using the *t* test. Changes in BCVA before and after treatment were tested using Wilcoxon–Matt–Whitney test. The change of CST and indicators of retinal blood flow from baseline were analyzed by paired *t* test. The comparison of different follow-up time indicators was performed by repeated measurement data analysis of variance. Statistical significance will be based on 2-sided tests, with *P* value less than .05 taken as the criterion for statisticalsignificance.

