### Study design and setting

2.1

This is a multicentre, randomised, equivalence, single-masked clinical trial set within specialized Eye Hospitals involving Hohhot Chao Ju Eye Hospital, Chifeng Chao Ju Eye Hospital, Baotou Chao Ju Eye Hospital, Datong Chao Ju Eye Hospital, Jining Chao Ju Eye Hospital and Bayannur Disabled Persons’ Federation Eye Hospital in China. It aims to evaluate the clinical effectiveness and safety of 6 + PRN IVC, when compared with 3 + PRN IVC, for the treatment of patients with DME.

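### The analysis section does not clearly specify a between-arm analysis of mean BCVA change, and the paired t tests assigned to CST and OCTA cannot compare the arms

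*Protocol article*

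**What the plan says.** The aim is comparative. Under Study design and setting: "It aims to evaluate the clinical effectiveness and safety of 6 + PRN IVC, when compared with 3 + PRN IVC". Allocation supports this: "All participants will be randomised 1:1 using computer-generated randomization". The primary outcome is "Mean change in BCVA on the study eye at both 24 and 48 weeks following treatment".

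The Statistical analysis section (2.11) then assigns methods:

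- **BCVA, summary:** "Quantitative data, BCVA, is represented by median (quartile), and other data is represented by mean and SD".
- **BCVA, test:** "Changes in BCVA before and after treatment were tested using Wilcoxon–Matt–Whitney test". The name as printed is not a standard one; I read it as Wilcoxon-Mann-Whitney.
- **CST and OCTA metrics:** "The change of CST and indicators of retinal blood flow from baseline were analyzed by paired", the sentence ending with the t test.
- **Follow-up times:** "The comparison of different follow-up time indicators was performed by repeated measurement data analysis of variance". No group or group-by-time term is named.
- **The only test expressly between groups:** "The comparison of clinical features between groups was performed using the" t test. Clinical features are not defined.

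**The concern.** A randomised trial answers its question through a contrast between arms. No sentence in section 2.11 clearly attaches such a contrast to the primary outcome, and the sentence that covers BCVA can be read as two different analyses. If that choice stays open, it can be made after the data are seen. Neither reading gives the between-arm difference in mean change that the primary outcome calls for.

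For CST and OCTA the wording is not ambiguous. A paired t test of change from baseline asks whether patients changed, not whether the regimens differ. Both arms receive the same active drug, so improvement in both is to be expected. If the two within-arm P values are all that is reported, the natural but unsound step is to compare them, and that step has no control of type I error.

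**Working it through.** The plan gives no numerical result for this point, so there is no figure to reproduce. Correlations, effect sizes and within-arm power below are assumptions. The group size of 50 is the evaluable number in the Sample size section.

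**1. BCVA, read as before versus after values.** The data are paired; the test assumes independence. Take equal variances σ² at both times and correlation r. The paired difference in means has variance 2σ²(1−r)/n; treating the values as independent gives 2σ²/n. The ratio of standard errors is 1/√(1−r).

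| r | 1/√(1−r) |
|---|---|
| 0.5 | 1.41 |
| 0.6 | 1.58 |
| 0.7 | 1.83 |

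This ratio is for means. A simulation of the rank test itself (normal data, n = 50, 4,000 runs, nominal two-sided 0.05, shift of 0.4 SD for power) agrees in direction:

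| r | Type I error, Mann-Whitney | Power, Mann-Whitney | Power, signed-rank |
|---|---|---|---|
| 0.3 | 0.020 | 0.48 | 0.63 |
| 0.5 | 0.005 | 0.48 | 0.77 |
| 0.7 | 0.001 | 0.49 | 0.93 |

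The test is too conservative and loses power. On this reading it also compares no arms.

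**2. BCVA, read as change scores compared between arms.** The same simulation set-up gives type I error 0.048. Asymptotic efficiency against the t test under normality is 3/π = 0.955. This is a valid randomised comparison. Two gaps remain. A rank test reported with medians does not estimate a mean change. And baseline BCVA, which is measured, is not used. In units of σ², the per-arm variance is 2(1−r) for change scores and 1−r² for ANCOVA:

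| r | Change score | ANCOVA | Reduction |
|---|---|---|---|
| 0.5 | 1.00 | 0.75 | 25% |
| 0.6 | 0.80 | 0.64 | 20% |
| 0.7 | 0.60 | 0.51 | 15% |

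**3. CST and OCTA, within-arm paired t tests.** Suppose the true change is the same in both arms and each within-arm test has power p. Exactly one arm is significant with probability 2p(1−p):

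- p = 0.8: 2 × 0.8 × 0.2 = 0.32
- p = 0.5: 2 × 0.5 × 0.5 = 0.50

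Simulation with n = 50 per arm and equal true change:

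| Change, in SD of change | Exactly one arm significant | Between-arm t test rejects |
|---|---|---|
| 0.2 | 41% | 5% |
| 0.28 | 50% | 5% |
| 0.4 | 33% | 5% |
| 0.8 | 0% | 5% |

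With a large change in both arms the two P values agree, but they still say nothing about the difference between regimens.

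**The case against.** The strongest reply is that section 2.11 may well contain a randomised comparison. Mann-Whitney is a two-sample test, so reading the BCVA sentence as change scores between arms is at least as natural as reading it as a misuse on paired data, and that comparison is valid. The t test of clinical features is expressly between groups, and the repeated-measures ANOVA could carry a group term. This stands in part: a reader might infer that the plan makes no randomised comparison of BCVA, and the text does not support going that far. It does not remove the point. Clinical features are undefined, BCVA and CST change have their own named tests, and the ANOVA sentence speaks only of follow-up times.

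Three further inferences should be resisted:

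- **That the ANOVA discards incomplete patients.** This is usual for the classical method, but the article states no missing-data rule, and that detail may sit in a document not shown. The same holds for confidence intervals not being mentioned.
- **That leaving out baseline makes the standard errors wrong.** Under randomisation an unadjusted comparison of change is valid; it is only less precise.
- **That the paired-data misuse creates false positives.** It does the opposite.

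It is also fair to say that the article nowhere announces that it will infer a regimen difference from significance in one arm only. The 32% to 50% is the risk if someone does so, and it vanishes when both arms change a great deal.

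**Conclusion.** The point holds as one of unclear and mismatched specification. For the primary outcome, the stated rule is either a test unsuited to paired data that compares no arms (standard error overstated 1.4 to 1.8 times at r = 0.5 to 0.7), or a valid rank comparison that does not estimate the declared mean change and gives up a 25% to 15% variance reduction over the same range. For CST and retinal blood flow, the stated test cannot compare 6+PRN with 3+PRN at all. This concerns what the article states, so it is more than condensed detail. The sizes rest on assumed correlations, equal variances, normal data and assumed within-arm power of 50% to 80%. That the arms go uncompared under the paired t tests needs none of those assumptions.

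**What to change.** Replace the BCVA sentence with one named analysis: the between-arm difference in mean BCVA change from baseline at both week 24 and week 48, adjusted for baseline BCVA, with 95% CI. Either ANCOVA at each time point, or a mixed model with arm, visit, arm-by-visit and baseline, would serve. Keeping both weeks leaves the primary outcome as written.

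Use the same analysis for CST. Use it for OCTA metrics too if a baseline is measured: Patient evaluation (2.8.1) mentions OCTA at 6 and 12 months only, and the assessment table is not shown.

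Report mean change and SD for BCVA alongside the medians. Keep a rank-based between-arm comparison of change as a sensitivity analysis, giving the test its correct name, and label the within-arm paired tests as descriptive. If repeated-measures ANOVA is kept, state its group and group-by-time terms.

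The cost is wording only. BCVA and CST need no new data, and the models can be run in the software already named. Recruitment had started (28 eyes by July 6, 2020), so the change should be dated and in place before outcomes are analysed.

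### The test named for change in CST and OCTA metrics is a paired before/after t test, which does not compare 6+PRN with 3+PRN, and no between-arm test is explicitly assigned to these two secondary outcomes

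*Protocol article*

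**What the plan says.** The aim is comparative. Study design and setting (2.1) states that the trial is to "evaluate the clinical effectiveness and safety of 6 + PRN IVC, when compared with 3 + PRN IVC", and Randomization (2.6) adds: "All participants will be randomised 1:1 using computer-generated randomization". Secondary outcomes (2.5.2) opens with "Mean change in CST in the study eye from baseline to both 24 and 48 weeks", followed by "Mean change in retinal microvascular metrics by optical coherence tomography angiography (OCTA)".

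Statistical analysis (2.11) links one test to these two outcomes by name: "The change of CST and indicators of retinal blood flow from baseline were analyzed by paired" t test. Two other sentences in that section could bear on them:

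- "The comparison of clinical features between groups was performed using the" t test. The section does not define clinical features.
- "The comparison of different follow-up time indicators was performed by repeated measurement data analysis of variance". It lists no variables and mentions neither a group factor nor a group-by-time term.

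All tests are two-sided at 0.05.

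**The concern.** The method does not match the question. A paired t test on change from baseline asks whether the mean change is zero. Here both arms receive conbercept, so CST can be expected to fall in each, and rejecting a zero change says nothing about whether six loading doses do more than three.

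If the test is run in each arm, the report will hold two P values and no estimate of the difference between regimens. Setting one P value beside the other is not a valid comparison, and it can mislead in two ways. With a modest response, chance alone can make one arm significant and the other not. With a strong response, both arms are significant and a real difference stays hidden. If the test is instead run on both arms pooled, the regimen drops out of the analysis altogether.

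At stake is the comparative reading of the main anatomical outcome (CST) and of the microvascular outcome (OCTA).

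**Working it through.** **Setting the sentences side by side**

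| Sentence in 2.11 | Names CST or OCTA? | Compares arms? |
|---|---|---|
| Paired t test | Yes, both | No |
| t test between groups | No; covers undefined clinical features | Yes |
| Repeated-measures ANOVA | No; variables not listed | Not stated; worded as a comparison of follow-up times |

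The one explicit assignment is therefore a test without an arm term. The one sentence that does compare arms is not tied to these outcomes.

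**What separate paired tests would show**

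The plan gives no figure to reproduce here: it states no SD, expected change or power for CST or OCTA. The calculation below is an illustration.

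Inputs:
- n = 48 per arm. Sample size (2.10) plans 60 per arm and 20% dropout; 60 × 0.8 = 48.
- Two-sided 0.05, from 2.11.
- True changes in units of the SD of change: assumed.

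*Power of a paired test in one arm.* Noncentral t with n − 1 = 47 degrees of freedom, noncentrality d√n, critical value 2.012.

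*Identical arms.* If each arm has power p, the chance that exactly one is significant is 2p(1 − p).

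| True change d, same in both arms | d√48 | p | 2p(1 − p) |
|---|---|---|---|
| 0.2 SD | 1.39 | 0.27 | 0.40 |
| 0.3 SD | 2.08 | 0.53 | 0.50 |
| 0.4 SD | 2.77 | 0.77 | 0.35 |
| 0.6 SD | 4.16 | 0.98 | 0.03 |

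A valid between-arm test would be falsely significant in 5% of such trials. The result depends somewhat on n: at 0.2, 0.3 and 0.4 SD the chance is 41%, 50% and 33% with 50 per arm, and 44%, 47% and 24% with 60 per arm. It fades once the change is large, so this error mainly threatens outcomes with a modest response.

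*Different arms, strong response.* Take true changes of 0.8 and 1.3 SD.
- Paired tests: noncentralities 0.8√48 = 5.54 and 1.3√48 = 9.01; each is significant with probability above 0.999.
- Between-arm t test of the same difference, 1.3 − 0.8 = 0.5 SD: noncentrality 0.5 × √(48/2) = 2.45 on 94 degrees of freedom, critical value 1.986, power 0.68 before any baseline adjustment (0.78 with 60 per arm).

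The paired results look the same in both arms, while the proper comparison would detect the difference in about two trials out of three.

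**The case against.** A reader might infer that CST and OCTA are tested only within each arm and never compared between regimens. The document does not support that. Section 2.11 does not say that the paired test is run by arm. Neither the between-group t test nor the ANOVA names CST or OCTA, but neither excludes them. CST is scheduled at baseline and at months 1, 3, 6 and 12 (Patient evaluation, 2.8.1), which makes it a natural candidate for the ANOVA, and arm could be a factor there. This is also a short section in a journal article, and lists of factors and variables commonly sit in the full protocol or the analysis plan.

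That objection stands as far as it goes: an unstated group term is not an excluded one, and its absence is not the finding. It does not remove the point. The article names a method, ties it to two named outcomes, and that method cannot answer the trial's question. An analysis plan that followed the sentence would carry the mismatch forward.

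Two further objections also stand. The effect sizes are assumed, and the false-contrast figures matter only if someone infers an arm difference from two separate P values, which the protocol does not say will be done. And both outcomes are secondary: the primary outcome is BCVA, and the sample size rests on an effective rate.

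**Conclusion.** Wrong as written; should be fixed. The test that 2.11 names for change in CST and OCTA metrics does not compare the randomised arms, and no between-arm test or estimate is explicitly assigned to them. The scope of the between-group t test and of the ANOVA is unclear.

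This conclusion rests on the wording and needs no assumed number. Its practical size does: with 48 per arm, about 35% to 50% of trials with identical arms show significance in one arm only when the change is 0.2 to 0.4 SD, and a 0.5 SD difference goes unseen when both arms respond strongly, against about 68% power for a direct comparison. Without an SD in the document, these figures cannot be turned into microns or into units of any OCTA metric.

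A higher grade is not warranted. The primary BCVA conclusion is not directly affected, and the CST comparison can still be made from scheduled measurements.

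**What to change.** Replace the paired-test sentence in 2.11 with, for example: *Change from baseline in CST and in each OCTA metric at weeks 24 and 48 will be compared between arms by a linear model with arm and the baseline value of that measure, reporting the adjusted mean difference (6+PRN minus 3+PRN) and its 95% CI. Within-arm changes will be presented descriptively.* A mixed model with arm, time and arm-by-time terms would serve equally well. If the ANOVA sentence was meant to provide this comparison, say so and name its outcomes and factors; likewise say what clinical features covers.

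Cost: for CST, wording only, since baseline and follow-up measurements are already scheduled and no more patients are needed. For OCTA, first confirm that a baseline scan is planned. Patient evaluation (2.8.1) mentions OCTA only at 6 and 12 months, and the assessment table is not reproduced in the text available, so this cannot be settled here. The present paired test needs that scan as well. The article reports 28 eyes recruited by July 2020, so at that date the wording could be corrected well before any analysis.
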